## Abstract

**Background:**

Patients with Parkinson’s disease often suffer from reduced mobility due to impaired postural control. Balance exercises form an integral part of rehabilitative therapy but the effectiveness of existing interventions is limited. Recent technological advances allow for providing enhanced visual feedback in the context of computer games, which provide an attractive alternative to conventional therapy. The objective of this randomized clinical trial is to investigate whether a training program capitalizing on virtual-reality-based visual feedback is more effective than an equally-dosed conventional training in improving standing balance performance in patients with Parkinson’s disease.

**Methods/design:**

Patients with idiopathic Parkinson’s disease will participate in a five-week balance training program comprising ten treatment sessions of 60 minutes each. Participants will be randomly allocated to (1) an experimental group that will receive balance training using augmented visual feedback, or (2) a control group that will receive balance training in accordance with current physical therapy guidelines for Parkinson’s disease patients. Training sessions consist of task-specific exercises that are organized as a series of workstations. Assessments will take place before training, at six weeks, and at twelve weeks follow-up. The functional reach test will serve as the primary outcome measure supplemented by comprehensive assessments of functional balance, posturography, and electroencephalography.

**Discussion:**

We hypothesize that balance training based on visual feedback will show greater improvements on standing balance performance than conventional balance training. In addition, we expect that learning new control strategies will be visible in the co-registered posturographic recordings but also through changes in functional connectivity.

**Trial registration:**

ISRCTN: ISRCTN47046299

## Background

Patients with Parkinson’s disease (PD) typically suffer from motor symptoms such as rigidity, tremor, bradykinesia, and postural instability, and are often confronted with serious mobility-related deficits such as problems with walking, balance, and transfers (e.g., standing up and sitting down, turning in bed). As the disease progresses, the patient’s functional capacity typically declines. This can severely impact activities of daily living [1], resulting in a downward spiral of immobility and deconditioning [2]. Impaired postural control is an important contributor to falls [3,4]. Physical therapy may positively affect mobility in PD, but exercises need to be task-specific and prescribed in sufficient dose [5-8]. In the case of impaired postural control this requires the inclusion of balance exercises in training programs [9].

A prerequisite for having patients fully involved and adhere to a training protocol is that the exercises are meaningful, engaging, and challenging. Novel technological developments allow for integrating a patient’s own movements in virtual environments, alongside other elements borrowed from the gaming industry, such as real-time 3D rendering, avatars, and score-keeping. Balance exercises are now often included in game consoles (such as Nintendo Wii™). Given the evidence that externally guided movements are mediated by neural pathways that differ from those involved in internally guided movements [10-12] and considering the extensive evidence regarding the benefits of using external stimuli in patients with PD [13-16] the provision of explicit, augmented visual feedback (VF) of a patient’s own movements in a virtual environment may be an important element in rehabilitation interventions in patients with PD.

To date, there are few reports on the additive value of VF to balance training paradigms for patients with PD. Esculier and co-workers [17] investigated the effects of home-based balance training using Nintendo Wii Fit and reported improvements in functional balance but a control group was not included. Pompeu and co-workers [18] did not find additional benefits of Nintendo Wii-based training compared to control therapy, but the contrast of the intervention between the groups was limited due to the fact that VF exercises only made up a portion of the therapy provided in the experimental group.

In the present randomized clinical trial (RCT) we will compare the effects of VF-based balance training on standing balance performance in patients with PD with the effects of conventional balance training. In addition, we will investigate to what degree the improvements in standing balance are accompanied by changes in cortical activity. To this end, we will employ whole-head electroencephalographic (EEG) recordings during a postural task [19,20].

We hypothesize that VF-based training is more effective than usual training in improving standing balance performance, with functional reach distance as the primary outcome. We also hypothesize that VF-related changes in balance performance are associated with more pronounced (movement-related changes in) beta synchronization in primary motor areas [21-23] and corresponding changes in functional connectivity of the entire motor network (including, e.g., pre-motor and supplementary motor areas), which may reflect the learning of novel strategies to control standing balance.

## Methods

### Design and procedures

This study is a pilot RCT comparing two treatment groups of patients with PD (Figure 1). Patients are allocated to either a five-week training program with balance exercises containing augmented VF (experimental group), or a five-week balance training program that follows existing guidelines (control group). Assessments will take place before intervention (T0), at six weeks (T1), and at twelve weeks (T2). Intervention assignment will be concealed by drawing opaque sealed envelopes by an independent investigator not involved in the study. A blinded researcher will perform the assessments. Patients will be asked to refrain from mentioning the nature of the intervention they receive to the researcher. All assessments will be performed in the ON-phase of levodopa medication. To minimize the effects of (changes in) PD medications on the patients’ physical performance, the time of day at which patients are assessed will be kept constant throughout the study.

**Figure 1 F1:**
[figure not shown]
Flowchart of the trial.

The protocol has been approved by the Medical Ethics Committee of the VU University medical center (VUmc) Amsterdam and is registered with Current Controlled Trials under ISRCTN47046299.

### Participants

A convenience sample of 36 patients will be recruited from the Neurology Department and from patient databases of the Department of Rehabilitation Medicine, VUmc. Patients who are likely to meet the criteria for inclusion will be invited to participate in the RCT.

Inclusion criteria will be (i) a diagnosis of idiopathic PD, mild to moderate stage (i.e. Hoehn & Yahr stages II and III), (ii) able to participate in either of the training programs, and (iii) written and verbal informed consent. Exclusion criteria are the presence of neurological, orthopedic, or cardiopulmonary problems that can impair participation, insufficient cognitive function (Mini Mental State Examination, MMSE < 24), an unstable medication regime, and any condition that renders the patient unable to understand or adhere to the protocol such as cognitive, visual, and/or language problems.

### Experimental group

In the experimental group VF will be integrated explicitly in each exercise. Three workstations (Motek Medical, Amsterdam, The Netherlands) will be set up in a gym. Figure 2 illustrates the key features of these workstations. They consist of a conventional PC with a 42" flat-panel LCD monitor and movement registration hardware. The latter will be used to map body movements to movements of an object (‘avatar’) on the monitor, by which patients can interact with balance games that are run on the workstations. Six different games will be used, each creating different challenges for the patient within a different virtual environment. Four games focus on controlling body position in space, one on stepping movement, and one on performing a sit-to-stand transfer movement. More accurate and/or faster control of the avatar results in accrual of points.

**Figure 2 F2:**
[figure not shown]
**Illustration of the intervention of the experimental group. A**: Setup of mobile workstation with force plate and/or inertial sensor. **B**: Screenshots of examples of balance games. See text for further details.

Movement registration will be accomplished using inertial sensors (Xsens, Enschede, The Netherlands) and a force plate (ForceLink, Culemborg, The Netherlands). Inertial sensors are attached to the patient’s chest using neoprene bands with a snap-on system, providing data about acceleration and rotation of the upper body. Monitoring the sit-to-stand transfer also requires an inertial sensor at the upper leg. The sensors can be easily transferred between patients throughout the training session. The force platform is used to obtain data about center-of-pressure displacements (COP).

The user interface on the workstations is deliberately kept simple and can be operated by a conventional mouse. Patients will receive detailed instructions about the operation of the software including the adjustment of game difficulty. They are encouraged to operate the workstations as autonomously as possible.

### Control group

Participants in the control group will receive equally-dosed balance exercises according to current guidelines for physical therapy in PD [9].

### Outcome measures

#### Descriptors

The MMSE, Hoehn and Yahr stage, disease duration, medication prescription and intake, and weight, length and leg length will be recorded during the first assessment.

#### Primary outcome measure

The Functional Reach Test (FRT) is used as primary outcome measure. The FRT measures the anterior limits of stability as perceived by the subject by assessing the maximal forward reaching distance. This outcome can be classified on the level of *activities* within the international classification of functioning, disability and health [25]. Lim and colleagues reported a mean score of 33.5 ± 7.4 cm in 26 patients with PD (range 22-50 cm) [14]. We note that for patients with PD the minimal detectable change is estimated to be between 9 [26] and 11.5 cm (smallest detectable difference) [27]. The test shows moderate inter- and intra-observer reliability [27,28].

#### Secondary outcome measures

To explore other effects related to training with augmented VF, secondary outcome measures related to balance and gait, the patients’ health status and their level of activity and participation, as well as measures derived from posturographic and EEG measurements will be assessed.

a) *Measures of balance and gait*: the Berg Balance scale assesses how well each of fourteen different balance-related tasks is executed [29]. The timed single leg test is a measure of how long the subject can maintain balance while standing on one leg [30]. The 10 m Walk Test will be used to record walking capacity at comfortable walking speed [26].

b) *Measures of patients’ health status and level of activity and participation*: parts I, II, III and IV of the Unified Parkinson Disease Rating Scale (UPDRS) will be assessed to evaluate disease severity and disease-specific impairments [31]. Items 13–15 and 29–30 of the UPDRS will be used to compute the posture and gait score subscore [15]. The Falls Efficacy Scale consists of ten questions related to the patient’s confidence not to fall during a number of everyday tasks [9,32]. The Parkinson’s Disease Questionnaire (PDQ-39) is a comprehensive questionnaire that provides a measure of health status along eight dimensions [33]. The Hospital Anxiety and Depression Scale addresses feelings of anxiety and depression related to being physically ill [34]. The Multidimensional Fatigue Inventory is a questionnaire developed to obtain insight into the level of fatigue [35].

c) *Posturographic outcome measures*: Tasks during posturographic evaluations consist of quiet stance and rhythmic tracking. Time series of the COP along anterio-posterior and mediolateral axes will be used to compute quantitative measures of task performance. In addition, stabilogram-analysis will be performed to investigate the dynamical and correlative structure of the data [36,37]. For quiet stance we will determine the COP’s variance, its temporal counterpart, the diffusion coefficient, as well as the scaling of the temporal correlation structure (the Hurst exponent). For rhythmic tracking we will follow the same approach but instead of the mere COP trajectory we will employ the distance between (the periodically moving) visual target and the COP in mediolateral direction (as displayed on the monitor). To specifically investigate effects on motor timing, we will also estimate the instantaneous relative phase between target and COP as well as the associated circular variance.

d) *EEG-related outcomes*: EEG will be recorded during the postural task. After artifact-removal based on independent component analysis [20], time-dependent EEG signals will undergo a conventional time-frequency analysis, followed by principal component analysis to identify significant changes in (frequency-dependent) motor-related potentials. We will further determine functional connectivity through neural synchronization in distinct frequency bands, i.e., the variance of the pair-wise relative phase between EEG signals. To localize the sources of brain activity we will combine the EEG signals with the co-registered anatomical MRIs and apply linearly constrained minimum variance beamformers [38,39]. Activities at the sources will finally be analyzed in the same form as the EEG signals at electrode level.

### Measurements and procedures

All assessment sessions will take place in a motion laboratory at VU University Amsterdam, Faculty of Human Movement Sciences. During each session the clinimetric assessments will be performed first, followed by combined posturographic and EEG recordings. An assistant will stand by at all times to prevent falls in the case of a loss of balance.

The clinimetric test battery has been tested extensively in a previous study [27]. The tests will be carried out in accordance with current guidelines [9,40].

An illustration of the combined posturographic and EEG recordings is provided in Figure 3. The patient will be asked to stand on a 600 mm × 400 mm force plate embedded in the floor (Kistler 9281B; Kistler, Ostfildern, Germany). A monitor providing feedback of the COP position is positioned at eye-height at a distance of ~75 cm from the subject. After familiarization with the setup the patient will perform twelve trials (4 conditions × 3 repetitions), with the possibility to rest after each trial. Each trial will consist of a sequence of 20 s quiet stance, 100 s rhythmic tracking, and 20 s quiet stance. During the rhythmic tracking segment a target will oscillate horizontally on the monitor at a frequency of 0.5 Hz. The patient is asked to match the target as accurately as possible by making whole-body swaying motions from side to side. VF of the COP will be provided by means of a black bar on the monitor. The experimental conditions during the swaying task will include conditions in which VF is withheld, is presented real-time, or is presented with a finite, constant delay of 250 or 500 ms (see Figure 3). From previous studies it is known that VF which is not provided to the subject directly (i.e. real-time) but with a finite delay, may destabilize performance on (tracking) tasks [41-43]. In that case, the better a subject is able to *decouple* from the VF (i.e., the less the subject relies/depends on visual information), the better he/she is able to perform the task. It should be noted that both the task and the VF during assessments will differ from what the patients experience during the training sessions.

**Figure 3 F3:**
[figure not shown]
**Illustration of measurement protocol for combined posturography and EEG recordings. A**: Setup of force platform and visual feedback. **B**: Experimental protocol. Each trial consists of a sequence of 20 s quiet stance, 100 s rhythmic tracking, and 20 s quiet stance. During quiet stance only a stationary target is shown. The rhythmic task will be carried out under four different visual feedback conditions: no feedback, real-time feedback, delayed feedback at 250 ms and delayed feedback at 500 ms. See text for further details.

During the postural tasks, 64-channel EEG recordings will be collected from Ag/AgCl electrodes that are placed on the scalp by means of a nylon head cap (TMSi, Enschede, The Netherlands). All signals will be high-pass filtered at 0.1 Hz and low-pass filtered at 100 Hz before being sampled at a rate of 2048 Hz (REFA amplifier, TMSi, Enschede, The Netherlands).

Anatomical MRI scans of the brain will be used to substantiate off-line source localization of the EEG signals. If a patient’s scan is not available, a new scan will be taken at VUmc, Department of Radiology.

### Sample size calculation

We calculated the sample size required to obtain sufficient power for finding a difference of 9 cm on the FRT. Pooled estimate of the common variance, calculated from data by Ashburn [44], was entered in a formula for two independent groups with paired observations [45]. A total sample size of twenty-four patients is necessary to find a difference between groups with at least 80% power. To account for smaller effect sizes and an estimated attrition rate of 10%, we plan to include thirty-six patients in total, eighteen in each group.

### Statistical analysis

Group differences in baseline patient characteristics will be tested using χ^2^-tests for categorical data and *t*-tests for continuous variables. Continuous outcome measures that are measured at all three time points will be tested for normality using the Shapiro-Wilk test. If assumptions for parametric testing are met, a mixed design ANOVA with between-subjects factor *group* (experimental vs. control) and within-subjects factor *time* (T0, T1, and T2) will be used to analyze the differential effect of the two interventions and the effect of time. If normality is rejected, or if outcomes are measured on the ordinal level, change scores between T1 – T0 and between T2 – T1 will be subjected to nonparametric Mann–Whitney U-tests. P < 0.05 will be set (two-tailed) as threshold for significance. Relative phase will be assessed through circular statistics using, in particular, Rayleigh tests to analyze group differences of relative phase uniformity between sources [46]. Correlation coefficients will be compared to investigate the association between outcomes.

Statistical analyses regarding EEG outcomes will be conducted using the methods outlined by Houweling and co-workers [47], with adaptations to EEG data regarding the accompanying lead field. Sources will be determined via pseudo *z*-scores of the beamformers that will be tested for within-group consistency through permutation tests [48]. The (relative) phases of the source projected EEG activity in the beta frequency band will be assessed through circular statistics (see above).

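### A Shapiro-Wilk result decides both the test and the contrast for the primary FRT, and the rank fallback asks different questions from the ANOVA and never tests T2 – T0

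*Protocol article*

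**What the plan says.** In the Protocol article, under Primary outcome measure: "The Functional Reach Test (FRT) is used as primary outcome measure". The FRT is a continuous distance in cm, assessed at T0, six weeks (T1) and twelve weeks (T2). The article gives it no analysis rule of its own, so the general rule under Statistical analysis governs it.

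That rule has three steps:

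- **Gate:** "Continuous outcome measures that are measured at all three time points will be tested for normality using the Shapiro-Wilk test".
- **Branch 1:** "If assumptions for parametric testing are met, a mixed design ANOVA with between-subjects factor" group and within-subjects factor time (three levels).
- **Branch 2:** "If normality is rejected, or if outcomes are measured on the ordinal level", then "change scores between T1 – T0 and between T2 – T1 will be subjected to nonparametric Mann–Whitney U-tests".

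For significance, "P < 0.05 will be set (two-tailed) as threshold for significance". No adjustment is stated for the two tests in Branch 2.

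**The concern.** A normality check that chose between two tests of the same contrast would be a small matter. Here it also changes the contrast.

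- **Branch 1** asks whether the arms differ in their course over all three visits: one test with 2 degrees of freedom.
- **Branch 2** asks two separate questions: do the arms differ in change from baseline to six weeks, and do they differ in change from six to twelve weeks? Change from baseline to twelve weeks, which is the retained effect, is not tested.

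If a benefit appears by T1 and is held, T2 – T1 contains no group difference. If it builds slowly, Branch 2 splits it into two small steps. If it appears and is then lost, a T2 – T1 result can be significant because of the loss.

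So which FRT question is answered, and with how many tests, is unknown until the outcome data have been examined. The two branches can also give different verdicts on the same data.

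**Working it through.** **No figure to reproduce on this point.** The article gives no error rate or switching rate for the gate. Its total of 24 patients is not in dispute here; the variance behind it is not printed.

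**Inputs from the article.** FRT mean 33.5 cm and SD 7.4 cm (Primary outcome measure); 18 per arm, 10% attrition, planned difference 9 cm (Sample size calculation); two-sided 0.05 (Statistical analysis).

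**Assumptions.** Exactly normal data; compound symmetry with between-visit correlation 0.5, 0.7 or 0.9; Shapiro-Wilk at 0.05; Branch 1 read as the group-by-time F test; Branch 2 counted as positive if either Mann–Whitney test has P < 0.05. There were 8,000 simulated trials per setting, so the Monte Carlo standard error is about 0.2 points at 5% (√(0.05 × 0.95 / 8,000)) and 0.5 points at 25%.

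**Step 1: how often normal data are sent to the rank branch.** If k tests were independent, the chance of any rejection is 1 − 0.95^k:

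- k = 1: 5%
- k = 3 (each visit, arms pooled): 1 − 0.95³ = 14.3%
- k = 6 (each visit and arm): 1 − 0.95⁶ = 26.5%

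| Per arm, correlation | 3 tests | 6 tests |
|---|---|---|
| 18, 0.5 | 13.6% | 26.0% |
| 18, 0.7 | 14.3% | 25.6% |
| 18, 0.9 | 11.8% | 22.2% |
| 16, 0.7 | 14.1% | 26.5% |

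Repeat runs at 18 per arm and correlation 0.5–0.7 gave 12–15% and 25–27%.

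**Step 2: type I error.** Over the same four settings, the ANOVA interaction rejects in 4.4–5.2% of trials and at least one Mann–Whitney test in 7.9–8.9%. Two independent tests would give 1 − 0.95² = 9.75%. The whole two-stage procedure rejects in 4.9–6.2%. This fits the mixture of branches: at correlation 0.5 with six tests, 0.740 × 4.9% + 0.260 × 8.9% = 5.9%, against 6.0% simulated.

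**Step 3: what the branches detect (18 per arm, correlation 0.5).** The effect is the difference between arms at T0, T1 and T2, in cm.

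| Effect | ANOVA | MW T1 – T0 | MW T2 – T1 | Either MW | Branches disagree |
|---|---|---|---|---|---|
| 0, 9, 9 | 96.8% | 93.0% | 4.7% | 93.7% | 4.7% |
| 0, 5, 5 | 52.5% | 48.0% | 4.6% | 50.4% | 17.5% |
| 0, 3, 6 | 56.4% | 20.8% | 20.6% | 40.1% | 24.5% |
| 0, 5, 0 | 52.6% | 47.4% | 48.4% | 65.0% | 14.2% |

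In the two sustained rows, T2 – T1 rejects at about its nominal 5%, because that contrast is null.

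**Step 4: the omitted contrast.** For the 0/3/6 effect, a Mann–Whitney test of T2 – T0 has about 62–64% power. A hand check agrees. The SD of a change score is 7.4 × √(2 × (1 − 0.5)) = 7.4 cm, so its standard error between arms is 7.4 × √(2/18) = 2.47 cm. A 6 cm difference gives 6/2.47 = 2.43 and power of about Φ(2.43 − 1.96) = 68% for a normal-theory test. A 3 cm difference gives 3/2.47 = 1.22 and about Φ(−0.74) = 23%. The rank branch runs the 3 cm comparison twice and the 6 cm comparison not at all.

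**The case against.** Much can be said for the rule as it stands.

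- **It is written in advance**, so no discretion is left over which branch to take. That stands, but the question answered still depends on the data.
- **How the check is run may be left to a fuller plan.** The wording points to the outcome values but does not rule out a check on residuals, and a single such test would switch in only about 5% of cases. This stands, and it is why a range is given. The contrasts in each branch, however, are fixed in the article.
- **At the planned effect it hardly matters.** "We calculated the sample size required to obtain sufficient power for finding a difference of 9 cm on the FRT", and at 9 cm both branches have over 90% power. This also stands. But the same section enlarges the sample partly to allow for smaller effects, and that is where the branches diverge.
- **The trial is called a pilot and a proof of concept.** That lowers the stakes, but the article still states a superiority hypothesis on the FRT.

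Three stronger readings are tempting and should not be drawn:

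1. *A treatment effect itself triggers rejection, because the pooled T1 data become a mixture of two distributions.* With SD 7.4 cm and 16–18 per arm, pooled T1 is rejected in 4.2–4.8% of simulated trials at 9 cm, against 4.8–5.1% with no effect. It rises to 12–13% only at 20 cm.
2. *The trial's error rate is badly inflated.* It is about 5–6% overall; the excess fits the two unadjusted tests in the rank branch.
3. *Shapiro-Wilk cannot detect skewness at this size.* Against a gamma distribution it rejects 23% (skewness 1) and 71% (skewness 2) with 16 values, and 46% and 98% with 32. Its sensitivity depends on how it is applied.

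**Conclusion.** The point holds, at moderate weight. The stated rule lets a preliminary test on the outcome data choose both the method and the contrast for the primary outcome, and the fallback does not match the main analysis: two unadjusted tests, no T2 – T0, and a T2 – T1 contrast that is null under a sustained benefit.

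Under exact normality the primary analysis would switch needlessly in somewhere between 1 in 20 and 1 in 4 trials, depending on a number of tests the article does not give. Once in the rank branch, the loss is greatest for a gradual benefit (0/3/6 cm). Averaged over both branches, power in that case falls only from 56.4% to 52.0–54.3%. The damage lies in the trials that switch, and in not knowing beforehand which question will be answered.

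The switching rates change little over correlations 0.5–0.9. The power figures rest on SD 7.4 cm, correlation 0.5, compound symmetry and assumed effect patterns, so they are illustrations, not forecasts.

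**What to change.** 1. Remove the normality gate for the FRT.
2. Name one contrast and one model as primary, whatever Shapiro-Wilk shows. The planned group-by-time analysis would do, as would a baseline-adjusted comparison at one named visit. The defect does not dictate which; the choice should follow the question the trial most wants answered.
3. Check residuals descriptively. Add a rank-based or permutation analysis of the same contrast as a sensitivity analysis.
4. Where rank tests are kept for ordinal outcomes, use T1 – T0 and T2 – T0, so that they match the question the ANOVA asks.

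The cost is a few sentences in the analysis section, settled before the outcome data are examined. No patients, visits or measurements change.

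### The named three-visit mixed ANOVA, as usually fitted without imputation, leaves out patients with a missing visit, including any with an observed T1 Functional Reach who miss T2, while 10% attrition is expected

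*Protocol article*

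**What the plan says.** The section Primary outcome measure states: "The Functional Reach Test (FRT) is used as primary outcome measure". Under Design and procedures the schedule is: "Assessments will take place before intervention (T0), at six weeks (T1), and at twelve weeks (T2").

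The section Statistical analysis sets two paths.

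- **Parametric path.** It begins: "Continuous outcome measures that are measured at all three time points will be tested for normality using the Shapiro-Wilk test". If the assumptions are met, "a mixed design ANOVA with between-subjects factor *group* (experimental vs. control) and within-subjects factor *time* (T0, T1, and T2) will be used".
- **Nonparametric path.** If normality is rejected, or the outcome is ordinal, "change scores between T1 – T0 and between T2 – T1 will be subjected to nonparametric Mann–Whitney U-tests".

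The section Sample size calculation foresees incomplete follow-up: "To account for smaller effect sizes and an estimated attrition rate of 10%, we plan to include thirty-six patients in total", that is, 18 per group.

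The article does not name an analysis set, an imputation method, or a rule for a patient with a missing visit.

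**The concern.** A classical between-within ANOVA works on one complete row of T0, T1 and T2 per patient. Without imputation, a missing T2 removes the whole row. A patient may complete the training, be measured at T1 and then not return six weeks later. That patient's T0 and T1 values are then lost to the primary analysis, although both were observed. Whether the immediate post-training result counts depends on attendance at a later visit.

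The two paths treat this patient differently. The Mann–Whitney test on T1 – T0 keeps the patient, and only the test on T2 – T1 loses them. For the FRT, the result of a normality test would therefore help to decide which randomised patients enter the T1 comparison.

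Precision is always at stake. Bias is at stake only if withdrawal after T1 is related to response and differs between the arms. Patients know which training they receive, and the article itself argues that gaming elements give extra incentive, so different adherence in the two arms is possible. The article gives no evidence that it will occur.

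**Working it through.** **Inputs from the protocol article.** 36 patients, 18 per arm; attrition 10%; required total 24 for 9 cm with at least 80% power (Sample size calculation). FRT SD 7.4 cm in 26 patients with PD (Primary outcome measure).

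**Assumptions, not in the article.** Within-patient correlation ρ of 0.5 or 0.7; all losses after T1; normally distributed change scores.

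**1. The plan's own sample size.** The variance used is not printed, so 24 cannot be strictly reproduced. Solving n = 2·SD²·(1.96 + 0.84)²/9² for n = 12 per arm gives SD = 7.87 cm (7.52 cm with the t distribution). Both are close to the quoted 7.4 cm, so 24 is plausible. Attrition alone needs 24/0.90 = 26.7, so 27; the rest of the 36 is the stated allowance for smaller effects.

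**2. Data discarded.** 0.10 × 36 = 3.6, so about 4 patients.
- FRT values observed if all 4 leave after T1: 36 × 3 − 4 = 104.
- Values in complete rows: 32 × 3 = 96.
- Discarded although observed: 8, namely 4 at T0 and 4 at T1.

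**3. Precision under random loss.** The SD of T1 – T0 is 7.4·√(2(1 − ρ)), which is 7.4 cm at ρ = 0.5 and 5.73 cm at ρ = 0.7.
- SE at ρ = 0.5 with 18 per arm: 7.4·√(2/18) = 2.47 cm.
- SE at ρ = 0.5 with 16 per arm: 7.4·√(2/16) = 2.62 cm.
- Ratio: √(18/16) = 1.06, a rise of 6% whatever ρ is.

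The estimate stays unbiased: in a simulation with a true difference of 5 cm, completers gave 4.95 cm and all patients with T0 and T1 gave 4.98 cm.

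**4. Bias under unequal, response-related loss.** Suppose every lost patient comes from the lower half of T1 – T0 change in their arm. The lower half of a normal distribution lies on average 0.80 SD below the mean: 5.9 cm at ρ = 0.5 and 4.6 cm at ρ = 0.7. Removing k of 18 such patients raises the arm's completer mean by d·k/(18 − k), where d is that distance.

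| Losses, experimental vs control | ρ = 0.5 | ρ = 0.7 |
|---|---|---|
| 2 vs 2 | 0 | 0 |
| 3 vs 1 | 5.9·(3/15 − 1/17) = +0.83 cm | 4.6·(3/15 − 1/17) = +0.65 cm |
| 4 vs 0 | 5.9·(4/14) = +1.69 cm | 4.6·(4/14) = +1.31 cm |

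Simulation with an assumed true effect of 3 cm agrees: about 3.7 to 3.8 cm for 3 vs 1, and 4.3 to 4.7 cm for 4 vs 0. If the losses fall mainly in the control arm, the sign reverses.

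**5. Extreme case.** If the four poorest T1 responders all leave one arm, a true difference of 0 is estimated as 2.7 cm (ρ = 0.5) or 2.1 cm (ρ = 0.7), and the type I error is about 21% instead of 5%. In a 300-run check with a true 5 cm at ρ = 0.5, a random-intercept likelihood model on all observed visits gave 5.15 cm at T1, against 7.86 cm for completers. Loss in that check depended only on observed values, which is the condition under which such a model works.

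**6. Power at the design difference.** With SD 7.87 cm and 9 cm (normal approximation), power falls from 92.9% at 18 per arm to 89.9% at 16 per arm.

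**The case against.** A reader might infer that the plan specifies a completers-only analysis. It does not. The article names a model and says nothing of complete cases or listwise deletion, and handling of missing data may be set out in a full protocol or SAP that is not shown. This part of the objection stands, so the point is limited to how the named method behaves as usually fitted.

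The timing of attrition is not given. A patient who leaves during the five weeks of training and misses T1 has no T1 value to lose. That also stands: four losses after T1 is the most that 10% attrition would imply, not a forecast.

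The bias figures rest on chosen scenarios, and equal or random loss gives none. Power at 9 cm is hardly touched, and 32 complete patients still exceed the 24 required. Both are correct. The 3 vs 1 shift is about a third of the standard error.

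Finally, different patient numbers for different tests are routine, and the trial describes itself as a pilot and proof of concept. This tempers the weight of the point but does not remove it. The method is one that the article fixes, attrition is foreseen, and a method that uses the observed values costs almost nothing.

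A reader might also infer that a mixed model would make both paths analyse identical patients. It would not. A patient who misses T1 but attends T2 has neither of the two change scores and stays outside both Mann–Whitney tests, while the mixed model would use that patient's T0 and T2.

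**Conclusion.** The point holds in limited form. The stated ANOVA, as usually fitted without imputation, excludes patients with any missing visit, including those with an observed T1 FRT, and nothing in the article offsets this. With four random losses after T1, the cost is about 6% in the standard error of the T1 contrast and no bias. With unequal losses concentrated among poor responders, the shift is roughly 0.7 to 1.7 cm. These figures assume SD 7.4 cm, ρ of 0.5 to 0.7 and all losses after T1; the article supports only the SD and the number lost. The larger shifts in the extreme case show the direction of the risk, not its likely size. The point is an improvement that should be made, not a flaw that invalidates the design.

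**What to change.** In Statistical analysis, replace the mixed-design ANOVA with a likelihood-based linear mixed model for repeated measures. Use group, visit and group × visit as fixed effects, a specified within-patient covariance, and a small-sample degrees-of-freedom correction such as Kenward–Roger, since there are only about 36 patients. State that all randomised patients are analysed in their allocated group with every available FRT value.

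The cost is a change of wording and the use of standard software, with no extra visits or patients. The model relies on data being missing at random, which is a weaker assumption than a complete-case ANOVA needs. The Mann–Whitney path can stay as it is, with the number of patients in each comparison reported.
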